**Methods/design:**

We will recruit 162 paediatric oncology patients and their families to a single centre randomised controlled trial. Patients from regional and remote areas, classified by Accessibility/Remoteness Index of Australia (ARIA+) greater than 0.2, will be randomised to a videotelephone support intervention or a usual support control group. Metropolitan families (ARIA+ ≤ 0.2) will be recruited as an additional usual support control group. Families allocated to the videotelephone support intervention will have access to usual support plus education, communication, counselling and monitoring with specialist multidisciplinary team members via a videotelephone service for a 12-week period following first discharge home. Families in the usual support control group will receive standard care i.e., specialist multidisciplinary team members provide support either face-to-face during inpatient stays, outpatient clinic visits or home visits, or via telephone for families who live far away from the hospital. The primary outcome measure is parental health related quality of life as measured using the Medical Outcome Survey (MOS) Short Form SF-12 measured at baseline, 4 weeks, 8 weeks and 12 weeks. The secondary outcome measures are: parental informational and emotional support; parental perceived stress, parent reported patient quality of life and parent reported sibling quality of life, parental satisfaction with care, cost of providing improved support, health care utilisation and financial burden for families.

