### Measurement

The SF-12v2 will be used to measure the primary outcome measure, parental health related quality of life. The SF-12 is a valid and reliable measure [30,31] used in a number of countries including Australia. More recently the SF-12 has been used in caregiver quality of life research [32].

Secondary outcome measures for parents will be: the informational/emotional subscale of the Medical Outcomes Study (MOS) Social Support Survey (a valid and reliable instrument for quantifying social support [33]), the 4-item Perceived Stress Scale (PSS) [34] and the FAMCARE scale (a valid and reliable instrument designed specifically to assess satisfaction with advanced cancer care [35]). For patients and siblings the Pediatric Quality of Life Inventory (Peds QL) parent proxy will be used (a valid and reliable measure of quality of life in children applicable to healthy populations and those with chronic disease [36]). In addition the Health Utilities Index Mark 2 (HUI2) will be completed by parents and used to assess patient quality-adjusted life years (QALYs).

Data collection will be undertaken via: user logs, chart audits, service database reviews, telephone and in-person interviews. Data collection with parents will begin at baseline (after consent has been obtained). The interviewer will be blinded to group allocation. Interviews will be used to obtain: demographics, baseline SF-12 scores, baseline informational and emotional support scores, baseline patient and sibling quality of life scores, and baseline satisfaction scores.

To reduce participant burden the completion of the various interview components will be staggered (Table 1). The initial interview will be the longest.

**Table 1 T1:** Interview schedule.

Component	Week												
	0	1	2	3	4	5	6	7	8	9	10	11	12
Demographics													
SF-12v2													
Informational/emotional support													
Perceived stress													
Patient quality of life													
Sibling quality of life													
HUI2													
Satisfaction													
Health care utilisation													
Family costs													

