#### Statistical analysis

Data analysis will be on an intention-to-treat basis and consist of univariate analysis between randomised groups on the primary and secondary outcomes. A more in-depth analysis will use longitudinal methods to account for correlations within families and to examine changes over time.

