- Families may also benefit financially from the improved support provided by the videotelephone service. Improved support has the potential to reduce the need for travel and associated costs. Information on family out-of-pocket expenses (such as travel costs including fuel, parking, fares; and other costs including meals, child care and accommodation) will also be obtained to assess the direct non-medical financial impact on families and how effectively the videotelephone service reduces this impact.

4. Cost-effectiveness analysis

- The health system perspective will be used for the primary analysis, and will be augmented in subsequent analysis with direct non-medical costs. The costs of providing the videotelephone service plus the total cost of health service use for the intervention group will be compared to the total cost of health service use identified in the regional and remote usual support control group. This is the incremental cost.

- Using the *Research Instruments *listed above, differences between the intervention group and the regional and remote usual support control group will be calculated. From this, the incremental cost per additional unit of benefit gained will be calculated, i.e. the incremental cost-effectiveness ratio (ICER); e.g. it costs an additional $x to improve parental quality of life by 1 point.

- A cost-utility analysis will also be undertaken. This allows comparisons between programs to be made and hence value for money judgements, as outcomes are standardised into quality-adjusted life years (QALYs). QALYs will be calculated using the HUI2 and the SF-6D algorithm to convert the SF-12 scores into utility scores (where 0 = dead, and 1.0 = best imaginable health state) and multiplied by the duration of life in that health state [37]. Differences in QALYs (for both parents and patients) between groups will be used to estimate the incremental cost-utility ratios.

- Sensitivity analyses will be conducted around the variables with the greatest uncertainty as well as the duration of final utility score at the end of the 12-week follow-up.

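### The cost-utility ratio rests on a QALY difference with no baseline-utility adjustment named; adjusting the parent analysis would gain precision with data already collected

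*Protocol article*

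**What the plan says.** In the Economic analysis section (item 4, Cost-effectiveness analysis), QALYs are built from HUI2 utilities for patients and SF-6D utilities derived from the SF-12 for parents, "multiplied by the duration of life in that health state". The estimator is then given in one sentence: "Differences in QALYs (for both parents and patients) between groups will be used to estimate the incremental cost-utility ratios". No regression model or covariate is named. The planned economic sensitivity analyses cover the most uncertain variables and how long the final utility is taken to last. They do not name baseline utility.

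The Statistical analysis section plans "univariate analysis between randomised groups on the primary and secondary outcomes" and adds: "A more in-depth analysis will use longitudinal methods to account for correlations within families and to examine changes over time". Neither sentence mentions a baseline covariate or refers to QALYs.

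The abstract says the SF-12 is "measured at baseline, 4 weeks, 8 weeks and 12 weeks". The Measurement section confirms the first of these: "Interviews will be used to obtain: demographics, baseline SF-12 scores". Baseline parent utility can therefore be derived. HUI2 is not in that section's list of baseline measures, and the marks in the interview schedule (Table 1) are not legible in the text at hand.

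The Randomization section describes allocation of regional and remote families by odd and even random numbers in sealed envelopes. It describes no blocking or stratification.

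**The concern.** A QALY total over 12 weeks is an area under the utility curve. If the week-0 utility is one of its points, a chance difference between arms at week 0 enters the QALY difference directly. It also enters indirectly, because families with higher utility at the start tend to have higher utility later. The described allocation method does nothing to limit such a gap.

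The QALY difference is the denominator of the cost per QALY. Twelve weeks is 0.23 of a year, so even a worthwhile utility gain yields only a few thousandths of a QALY, and a shift of similar order can move the ratio a long way. The abstract gives cost-effectiveness as the primary aim, so avoidable noise in this quantity is worth removing. Any adjustment of the week-12 SF-12 comparison would not do this, because the QALY is a separate outcome.

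**Working it through.** **Inputs from the protocol article.** 54 families per randomised arm (Sample size calculations); SF-12 at weeks 0, 4, 8 and 12 (abstract); MCS-12 target difference 7.5 with SD 10, that is 0.75 SD; one SEM 3.74, that is 0.374 SD.

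**Inputs assumed, because the documents do not give them.** Utility SD 0.10-0.15; correlation ρ between any two visits 0.5-0.7 (compound symmetry); QALY by the trapezoid rule; a utility gain of 0.05 at week 12 as an illustration.

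**The plan's own figure.** No QALY effect or precision is stated, so there is none to reproduce. The arm size does reproduce: 2 × (2.576 + 1.282)² × (10/7.5)² = 52.9, or 53 per arm by the normal formula, and 54 per arm gives 90.7% power (89.6% with the noncentral t). Nothing below changes that.

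**Step 1: weights.** Trapezoid weights in years are 2/52, 4/52, 4/52 and 2/52, which sum to 12/52 = 0.231.

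**Step 2: chance gap at baseline.** SE = SD × √(2/54) = 0.192 × SD, which is 0.019 for SD 0.10 and 0.029 for SD 0.15.

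**Step 3: carry-over into QALYs.** Expected shift = gap × (2 + 10ρ)/52.
- Lowest: 0.01925 × 7/52 = 0.0026 (SD 0.10, ρ = 0.5).
- Highest: 0.02887 × 9/52 = 0.0050 (SD 0.15, ρ = 0.7).

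**Step 4: comparison with an effect.** A gain rising linearly to 0.05 has weight (4 × 1/3 + 4 × 2/3 + 2)/52 = 6/52 and is worth 0.05 × 6/52 = 0.0058 QALY. If the gain is fully reached by week 4, the weight is 10/52 and it is worth 0.0096. The one-SE shift is below the effect in every case. With the linear gain and the incremental cost held fixed, a one-SE gap against the intervention leaves 0.0032 to 0.0008 QALY. It multiplies the cost per QALY by 0.00577/(0.00577 − 0.00259) = 1.8 up to 0.00577/(0.00577 − 0.00500) = 7.5. A gap at least that adverse has a chance of about 16%.

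**Step 5: how often the carried gap matches the whole effect.** Taking the MCS-12 effect in SD units as a stand-in for utility, the probability in either direction is:

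| Effect | Time course | ρ = 0.5 | ρ = 0.7 |
|---|---|---|---|
| 0.75 SD (planned) | linear | 0.1% | 0.9% |
| 0.75 SD | reached by week 4 | <0.1% | <0.1% |
| 0.374 SD (one SEM) | linear | 10% | 20% |
| 0.374 SD | reached by week 4 | 0.6% | 3.1% |

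**Step 6: gain from adjustment.** The variance of the QALY total is SD² × [40(1 − ρ) + 144ρ]/52². Its squared correlation with baseline is (2 + 10ρ)²/[40(1 − ρ) + 144ρ].
- ρ = 0.5: 49/92 = 0.53, so the SE is multiplied by √0.47 = 0.68, a cut of 32%.
- ρ = 0.7: 81/112.8 = 0.72, so the SE is multiplied by √0.28 = 0.53, a cut of 47%.

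Across the assumed ranges, the SE of the QALY difference falls from 0.0035-0.0059 to 0.0021-0.0036.

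**The case against.** The strongest objection is that the article does not prescribe a crude difference. A baseline-adjusted difference is also a between-group difference, and a condensed article may leave the QALY regression to a full protocol or analysis plan that is not shown. This stands: a reader might infer that the authors have chosen an unadjusted estimator, but the text says only that no adjustment is named. The univariate rule points towards an unadjusted one without settling the matter. It covers the primary and secondary outcomes, and QALYs are not in the abstract's list of these.

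A reader might also infer bias. That is not supported. Under randomisation the unadjusted difference is unbiased, and a correctly calculated standard error already allows for chance imbalance.

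A reader might infer that the baseline gap will typically swamp the effect. Step 5 does not support that for an effect of the planned 0.75 SD, where a matching gap has under a 1% chance at these correlations. The linear rise is also unfavourable to the plan: nurse calls are most frequent in the first four weeks, so benefit might come early. Against that, 0.75 SD is a target for the parental mental component score, and no utility effect is planned for parents or patients.

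Finally, the economic section also plans cost per point of benefit, so the cost-utility ratio is only part of the cost-effectiveness aim. The patient half cannot be checked, because week-0 HUI2 is not confirmed.

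What remains is that the baseline covariate for parents is already in hand and using it costs almost nothing.

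**Conclusion.** The point holds as an improvement in precision and protection against chance imbalance. It does not show an error or a contradiction in the plan. Without adjustment, the variance of the QALY difference would be roughly two to three and a half times what it need be (1/0.47 = 2.1 to 1/0.28 = 3.5). A baseline gap of ordinary size would move the difference by 0.0026-0.0050 QALY, against 0.0058 for the illustrative gain. A gap as large as the whole effect is unlikely for an effect of 0.75 SD. It is plausible for one near one SEM that emerges gradually.

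These sizes rest on an assumed utility SD, correlation structure, trapezoid QALY and effect, none of which is in the documents. The time points are documented for the SF-12 only, so the figures apply to parents and carry over to patients only if HUI2 follows a similar schedule. The stated sample size and equivalence power are unaffected. Adjustment narrows the uncertainty but does not remove it: an SE of 0.0021-0.0036 is still large beside 0.0058.

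**What to change.** Add to item 4 of the Economic analysis section that the incremental parent QALY for the two regional and remote arms is estimated by regressing 12-week QALY on arm and week-0 SF-6D utility. State that this adjusted difference is used in the incremental cost-utility ratio, with the unadjusted difference reported beside it. Specify the same for patients with week-0 HUI2, after confirming that HUI2 is asked at baseline.

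The cost is one or two sentences. The parent analysis needs no new data, since baseline SF-12 is already collected. The patient analysis needs a check of the interview schedule. If a full analysis plan already specifies this adjustment, a reference to it is enough.

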## Discussion

In 2001, over 600 children were diagnosed with cancer in Australia [43]. By 2011, the incidence of childhood cancer is projected to increase by 7% for females and 5% for males [44]. The cumulative toll on these children and their families is high, socially, psychologically and economically. They have a greater risk of developing psychological and emotional difficulties than other children and families [45]. The support provided by specialist health professionals, the continuity of follow-up care and the support provided by family members have been identified as critical factors [46].

Improving the specialist support provided to these families has the potential to increase the quality of life of the entire family through: improved symptom identification and management, the provision of information, education and counselling, and better continuity of care. This may also reduce the need for these families to access local health care services for reasons that can be avoided with improved specialist support. It also has the potential to reduce some of the economic burden these families face through reductions in unnecessary travel.

The use of videotelephony will overcome many of the issues associated with providing improved support at a distance including the availability of experienced specialist health care professionals in regional and remote areas, and accessibility difficulties due to distance, time, cost and transport.

This work will present a new and innovative use of videotelephone technology as well as a new method for supporting regional and remote oncology patients and their families. The completion of a large randomised controlled trial will add significantly to the small evidence base for home telehealth [47]. It will be the first study of its kind in paediatric oncology. With the inclusion of a comprehensive economic evaluation, it will set an international benchmark as very few studies in home telehealth include cost-effectiveness or cost utility analyses [48]. It will also assist with the application of this model of support in other health care contexts.
